## Abstract

Leadership is an essential skill for success in nursing practice, influencing the nursing team’s organization, the quality of health services and decision-making in complex situations. The COVID-19 pandemic has further highlighted the need for leadership in nursing, with nurses playing a crucial role in addressing the crisis. However, there are challenges in leadership training, with conventional expository class methods often neglecting this skill. This study proposes to evaluate the impact of an online educational module focused on leadership for Nursing students, recognizing the importance of training future professionals from the beginning of their careers. To present a study protocol to evaluate the effect of an online educational module in comparison with a conventional expository class related to knowledge acquisition by Nursing students on the topic of Leadership. A Randomized Controlled Study, single-blind, two-arm will be conducted. Sixth semester students regularly enrolled in the nursing course will take part in the study. Participants will be randomly distributed into two groups, namely the Control Group, which will undergo a conventional class, and the Experimental Group, which will undergo an online educational module. Two important moments will be considered to evaluate the results of the intervention. A pesquisa, em fase de design, terá resultados, conclusões e análises definidos após a coleta de dados. The primary outcome is expected to demonstrate that the online module is equal to or superior to the conventional module in the acquisition of knowledge about leadership, addressing topics such as team involvement, organizational culture, conflict management and feedback. The secondary outcome will assess the acquisition of knowledge about leadership through an adaptation of the Nursing Student Self-Perception Questionnaire in the Exercise of Leadership.

## Introduction

Nurses assume a wide range of responsibilities in the context of healthcare services, from direct patient care to administrative, management, educational and research tasks. They are tasked with managing patient care and coordinating healthcare facility operations. Leadership is fundamental in all of these activities, being recognized as an essential skill for successful nursing practice [1].

Leadership in Nursing is a dynamic skill which can be cultivated and strengthened over time. Studies such as the one by Varanda *et al.* (2023) [2] highlight the direct relationship between leadership and team organization, highlighting its importance for developing quality health systems and improving patient care.

The act of leading accompanies nurses in any of the fields in which they work. Nurses are challenged to deal with complex situations, analyze information and make assertive decisions to ensure the safety and well-being of patients, as well as their team. The ability to lead is essential to face the constantly changing challenges in the healthcare environment and provide quality care [3].

Faced with the real need to encourage development of leadership in Nursing, the World Health Organization (WHO) in partnership with the International Council of Nurses (ICN) launched the “Nursing Now Challenge” in 2018. The Program was strengthened in Brazil through the partnership between the Federal Nursing Council (*Conselho Federal de Enfermagem - COFEN*) and the OMS/OPAS, with one of the campaign’s primary goals being to strengthen the education and development of Nursing professionals with an emphasis on leadership [4].

Nursing leadership during the COVID-19 pandemic was tested on different fronts, requiring specific skills to face unprecedented challenges. As the largest professional category in healthcare, nurses have not only assumed clinical responsibilities, but also led teams, managed resources and provided emotional support amidst a scenario of great stress and uncertainty. Thus, leadership has emerged as an essential element in maintaining the cohesion and effectiveness of healthcare teams during this challenging period [5].

There are still challenges in implementing leadership teaching in the training of nurses 22 years after the promulgation of the Curricular Guidelines for the Undergraduate Nursing Course. This occurs due to the outdated use of teaching methodologies, the fragility of teaching related to the lack of updating of teachers regarding teaching leadership and educational methods which have roots in conventional and traditional education [6].

As a way of mitigating the deficiency in teaching regarding the subject and given the possibility of exploring what digital educational technologies can provide to the learning process, the paradigm of teacher-centered education is broken and begins to value the student, providing an education capable of promoting meaningful learning [7].

Considering the above, there is a need to evaluate the effect of an online educational module in comparison with a conventional expository class related to knowledge acquisition by Nursing students on the topic of Leadership.

## Materials and methods

This protocol will adhere to the Consolidated Standards of Reporting Trials (CONSORT) [8] and standard protocol item statements for randomized trials [9]. This study was approved by the Research Ethics Committee of the Universidade Federal do Rio Grande do Norte - UFRN, under CAAE No. 75851023.0.0000.5537 and Registry: RBR-2dfqmr2 - Registro Brasileiro de Ensaios Clínicos – REBEC (26/02/2024).

### Study design

This is a Randomized Controlled Study in which participants will be selected at random and the study will be conducted in a single-blind manner, with assessments before and after the intervention. To do so, participants will be divided into a Control Group, which consists of subjects whose performance in relation to a dependent variable is used as a parameter to evaluate behavior; and the Experimental Group is the group of participants who receive the intervention [10]. Participants in the Control Group will undergo a conventional class while the other participants in the Experimental Group will undergo an online educational module.

### Study scenario

Recruitment and intervention will be conducted at the Nursing Department of the Federal University of Rio Grande do Norte (UFRN), Campus Natal/RN, Brazil, with undergraduate Nursing students from this institution.

### Selection criteria

Person of both sexes, aged 18 or over; be a student in the sixth semester of the UFRN Nursing course. Students in the sixth semester who have already attended other degrees, *stricto sensu* or *lato sensu* postgraduate courses, extension courses, free courses, short duration courses, or events that address the topic of leadership and absentees will be excluded from the study.

### Recruitment

Sixth semester students will be recruited by offering a 30-hour “Nursing Leadership Course” extension course, registered in the institution’s Integrated Academic Activities Management System (SIGAA).

Firstly, students in the sixth semester of the undergraduate nursing course at the Federal University of Rio Grande do Norte will be invited via the class Whatsapp group, encouraging them to sign up for the course.

Interested students will have to fill in a registration form available on the Google Forms platform, which will collect initial information and confirm their interest in taking part in the study. During registration, participants will agree to the Informed Consent Form (ICF), ensuring that they are aware of the stages of the study.

After registration, a Google Meet call will be scheduled with all registered students. During this call, a pre-test will be administered to assess prior knowledge about leadership. Participants who complete the pre-test and confirm their adherence to the study will be added to a WhatsApp group to receive important notices and information about the course.

In order to minimize interaction between the control and experimental groups, participants will be given clear instructions on the importance of not sharing information between the groups, with the aim of preserving the integrity of the study, since they will be part of different Whatsapp groups but will not know which group they have been allocated to.

### Allocation

To ensure random allocation into groups, simple randomization will be applied using the website www.random.org. This tool will perform the randomization completely randomly, without researcher interference, ensuring that all participants have an equal chance of being assigned to either the control group or the experimental group.

Although the participants self-selected when they enrolled, randomization was carried out after the enrolments were collected, with the aim of ensuring that everyone had the same chance of being allocated to the different experimental groups.

Participants in the control group will attend a conventional expository class, held in person at the Nursing Department. The class, conducted by the researcher, will last four hours in the afternoon and cover the same topics as those addressed in the online educational module. Both the experimental group, which will have access to the online module, and the control group, which will have access to the conventional class, will last 30 hours. The control group will attend a lecture given by the researcher, covering the same topics and in the same depth as the online module at the Nursing Department at the Federal University of Rio Grande do Norte, lasting four hours. Although the in person class will last four hours, the total workload for the control group will also be 30 hours, as there will be suggested supplementary reading to be consumed.

Meanwhile, participants in the experimental group will engage in an online educational module, with recorded classes hosted on the Google Classroom virtual learning environment. Participants will have a period of five days to access and consume the module’s content, totaling 30 hours, from registration to completion. After the class, all the participants in the research, both the control group and the experimental group, will be called to go in person to the Nursing Department of the Federal University of Rio Grande do Norte to complete the post-test and receive certification of participation in the course.

It is important to emphasize that participant allocation will be conducted in a single-blind manner to ensure impartiality in the process. The sample for this study will be divided equally between the two groups, ensuring that both the Control Group and the Experimental Group have an equivalent number of participants. Additionally, participant assignment will remain confidential to prevent any external interference or bias from the researcher or third parties.

### Initial evaluation

The researcher will approach students virtually. Participants who agree to be part of the study, by signing the Informed Consent Form, will be added to a WhatsApp group where necessary notifications will be sent. After the registration is complete, participants will be introduced to the study and informed about the interventions.

Any questions related to the research will be clarified before the start of the interventions. Subsequently, participants will be assigned to one of the two groups (Control Group or Experimental Group) based on a randomization list.

### Intervention

The sample will consist of approximately 40 students from the sixth semester of the Nursing course who are regularly enrolled. Throughout their participation, both online and in person, the participants will use exclusively their own mobile devices and internet access for registration and the pre-test.

The pre-test will be administered via Google Forms, and no prior support materials will be provided. Participants will have 20 minutes to complete the pre-test, which will be conducted by the researcher using a Google Meet room as the virtual space to accommodate all participants, as everyone needs to answer the pre-test synchronously within the estimated 20 minutes. The virtual tool’s chat feature will be used to signal completion. All participants must respond within the allocated time.

Randomization will be conducted only with participants who complete the pre-test and meet the eligibility criteria. These students will be randomly assigned to either the Control Group or the Experimental Group. After randomization, participants will be informed via WhatsApp and email about which group they belong to: those attending the in-person course at the Nursing Department or those consuming the online educational module.

Participants in the Experimental Group will be enrolled in a Google Classroom course by the researcher, with instructions sent via email and WhatsApp. The online educational module, consisting of interactive recorded classes, will have a duration of four hours, with additional content such as digital materials, quizzes, and forums. Topics covered include team motivation and engagement, organizational culture, conflict management, and constructive feedback. Participants will have flexibility in accessing the classes and will not be restricted by geographical location.

The Control Group will attend a conventional expository class held in person at the Nursing Department of the Federal University of Rio Grande do Norte. The class will use visual materials, such as PowerPoint presentations, covering the same topics as the online module with equal depth and breadth.

The Experimental Group will also attend the Nursing Department in person after the Control Group’s activities. Following this, both groups will complete the post-test online via Google Forms. Participants will use their own electronic devices and access the UFRN internet. They will have 20 minutes to complete the post-test. After completion, all participants will receive a certificate of participation in the course and will be released.

Thus, the pre-test will be conducted synchronously and remotely, before the intervention, using Google Forms, with participants gathered in a Google Meet room, 20 minutes and no prior support material will be provided. After the pre-test, participants will be allocated and randomized into groups. The post-test will be conducted after all planned interventions are completed, in person using Google Forms. Participants will again have 20 minutes to complete the questionnaire. The researcher will be present during the application to ensure that all participants have the same conditions of time and environment to complete the test.

The purpose of the evaluation is to assess the effectiveness of an online educational module on leadership in the knowledge acquisition of Nursing students.

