### Data collection instrument

To evaluate the effectiveness of the module and the acquisition of knowledge by the participants, a form developed in Google forms will be used, applied as a pre-test and post-test for both the control group and the experimental group.

The data collection forms will consist of two documents. The first is the registration form with demographic characterization, which will collect personal and academic information relevant to the study; while the second is a form that will be used as a pre- and post-test containing a problem situation made up of four objective questions focused on topics such as team motivation and engagement, organizational culture, conflict management and constructive feedback, in addition to the adaptation of the Nursing Student Self-Perception Questionnaire on Exercising Leadership (QUAPEEL), developed by Cardoso, Ramos and D’Innocenzo (2014) [11].

The problem situation is made up of six objective questions, and each question contains four alternative answers. The questions in the document are: ‘Faced with the possible dismissal of nursing professionals due to the salary floor, how would you, as a leader, address this issue to keep the team motivated and engaged?’; ‘Faced with signs of stress in the team, how would you promote an organizational culture that effectively addresses work overload and preserves the well-being of professionals? ‘; ‘In an environment where conflicts can arise due to difficult ethical decisions, as a leader, how would you mediate a conflict between team members with opposing views on the allocation of scarce resources?’; ‘As a leader, how would you provide constructive feedback to team members who have made medication errors, while promoting professional development?’; ‘How do you conceptualize leadership?’; ‘Do you consider yourself a leader?’; ‘Tick the interpersonal skills you consider necessary for a leader?’

QUAPEEL is a questionnaire that measures the skills and attitudes that nurses should exercise in their leadership practice. For use in this study, the questionnaire will be adapted in the section referring to the sociodemographic question, since the instrument will be applied to students and not to nurses.

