On the other hand, if the data does not follow a normal distribution, the Wilcoxon test for paired samples will be used, which is a non-parametric test suitable for comparing the medians between the two moments. The aim of both tests is to assess whether the changes observed between the pre- and post-test are statistically significant.

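### Pre-to-post change within an arm mixes learning with recall of a repeated form and a change of test setting, so the planned paired tests cannot show that the teaching worked

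*Protocol article*

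**What the plan says.** The protocol article describes the two testing occasions under Intervention. For the first, "the pre-test will be conducted synchronously and remotely, before the intervention, using Google Forms, with participants gathered in a Google Meet room". Students use their own devices and internet connection, have 20 minutes, and report completion in the chat. The session is one "which will be conducted by the researcher using a Google Meet room as the virtual space to accommodate all participants". For the second, "The post-test will be conducted after all planned interventions are completed, in person using Google Forms", again with 20 minutes, on students' own devices but over the university network. There, "The researcher will be present during the application to ensure that all participants have the same conditions of time and environment to complete the test".

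Under Data collection instrument, one form serves both occasions: "the second is a form that will be used as a pre- and post-test containing a problem situation", together with the adapted QUAPEEL self-perception questionnaire. No parallel version is described. The interval between the tests is not stated. The nearest guide is in Allocation, for the online arm: "Participants will have a period of five days to access and consume the module’s content".

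Data analysis says that effectiveness is measured by the pre-test and the post-test. It names a paired t-test, or a paired Wilcoxon test if the data are not normal, and adds: "The aim of both tests is to assess whether the changes observed between the pre- and post-test are statistically significant". The Primary outcome section, by contrast, frames the aim as a comparison of the online module with the conventional class.

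**The concern.** A paired test asks whether the mean change differs from zero. It attributes the change to teaching only if nothing else moves the score between the two readings. Here two other things do change. The students have already seen the items, and the knowledge part is a handful of closed questions with four alternatives each. The setting also moves from remote to in-person oversight. Only the form and the 20-minute limit stay fixed.

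Recall would tend to raise the second score. If students looked things up or conferred at the remote pre-test, that would raise the first score and shrink the change. The net direction is unknown. What is at stake is the wording of the conclusion: a report that follows the Data analysis section could call either method effective on a change that teaching did not cause, or could miss a change that it did cause.

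**Working it through.** **No figure to reproduce.** The document gives no SD, effect size, alpha or power, and the sample of about 40 is one of convenience. The sizes below are illustrations.

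**Inputs from the document**
- About 40 students divided equally, so n = 40 / 2 = 20 per arm (Study population; Allocation).
- Paired t-test of pre against post (Data analysis).

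**Assumed inputs**
- Two-sided alpha 0.05.
- Knowledge scored as number correct, with an SD of the change of 1.2 items.
- No learning in either arm.
- A common retest and setting gain g of 0.2, 0.3 or 0.5 items.

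**Paired test within one arm.** The test has n − 1 = 19 degrees of freedom and critical value 2.093. Its noncentrality is (g / SD) × √n, with √20 = 4.472. The rejection rate is the noncentral t probability beyond ±2.093.

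| Gain g (items) | g / SD | Noncentrality | Rejection rate, n = 20 |
|---|---|---|---|
| 0 | 0 | 0 | 5.0% |
| 0.2 | 0.167 | 0.75 | 10.9% |
| 0.3 | 0.250 | 1.12 | 18.6% |
| 0.5 | 0.417 | 1.86 | 42.4% |

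The text does not say whether the paired test is run by arm or on all students together. If all 40 were pooled, the rates for the three gains would be 17.7%, 33.8% and 72.9%.

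**The same check in SD units.** With n = 20 and no learning, shifts of 0.2, 0.3, 0.5 and 0.8 SD of the change give rejection rates of about 14%, 25%, 56% and 92%.

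**Between-arm comparison under the same shifts.** If both arms gain g, the expected difference in mean change is g − g = 0. A simulation of 40,000 trials, using a two-sample t-test on change scores with 20 per arm, rejected in 4.9% to 5.1% of trials at every shift from 0 to 0.8 SD.

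**Why comparing two paired results does not help.** A reader could try to compare the methods by noting which arm reached significance. In the same simulation, with identical arms and no learning, exactly one arm was significant in 9.6% of trials with no shift, 23.7% at 0.2 SD and 48.9% at 0.5 SD.

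**The case against.** The strongest reply is that this is a randomised trial whose stated aim is a comparison between arms. Both arms take the same form together, remotely before and in person afterwards, with equal time. Recall and setting are then common to both and largely cancel, and using one instrument twice is a coherent choice. This stands, and it limits the point. It does not remove it, because the tests that the article actually specifies are paired and are aimed at the pre-to-post change.

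Three stronger readings might be inferred, and the document supports none of them.

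- *The comparison of the arms is biased.* The pre-test precedes randomisation, so look-up there can only add noise to a baseline covariate. Nothing in the text suggests that recall differs by arm.
- *The pre-test is unsupervised.* The researcher runs it live over Google Meet with a time limit and no support materials. The contrast is remote against in-person oversight, and students use their own devices on both occasions.
- *Students keep the questions for a known number of days.* The text does not say whether the form stays open or whether items or scores remain visible. It gives only the module's five-day window, not the interval between tests.

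Nor does the article contradict itself on equal conditions: that assurance concerns all participants at the post-test. Look-up is a concern for the knowledge questions, and hardly for QUAPEEL, which asks for self-perception.

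**Conclusion.** The point holds as a limit on what the named tests can show. A significant pre-to-post change within an arm cannot separate learning from recall of the items and the change of setting. With 20 per arm, an SD of change of 1.2 items and no learning, a gain of 0.2 to 0.5 items raises the chance of a significant paired test from 5% to between 11% and 42%. Those gains and that SD are assumptions. The true shift could be smaller, or could run the other way if look-up at the pre-test outweighs recall. The randomisation is not undermined, and a between-arm analysis stays at about 5% for any shift common to both arms. The matter should be corrected because it decides whether the trial's conclusion on effectiveness is supported by its own analysis.

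**What to change.** **In Data analysis**, state that pre-to-post change within each arm is descriptive and is not evidence that the teaching worked. Base the effectiveness conclusion on the comparison between arms, for example the post-test score compared between groups with adjustment for the pre-test score. This costs a few sentences and no new data.

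**Where feasible**, hold the pre-test at the Nursing Department under the same in-person supervision as the post-test. Close the form afterwards without releasing answers or scores. The cost is one extra attendance before randomisation, which may deter a few volunteers. The article says that the study is still being prepared for recruitment, so the change is possible now and cannot be made after data collection. If the remote pre-test is kept, report the difference in setting as a limitation of any within-arm change.

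A second, counterbalanced scenario at post-test is not recommended. The arms do not exist when the pre-test is taken, so form order could not be balanced within them without stratifying the randomisation. The two versions would also not be equated, and the added variation would fall on a very short test.
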